#### Stage 1 participants

2.3.1

The eligibility criteria for participants in Stage 1 of the study is shown in Table 1. Recruitment of people with intellectual disability will adhere to the inclusive approaches in section 2.1.3. Family members and support people, healthcare providers and disability sector stakeholders will be identified through the researchers’ professional networks and the Advisory Group. Potential participants will be emailed a link to an accessible project summary and a secure form to provide their name and telephone number. Healthcare providers will be able to opt to continue to the online consent form with an email alert sent to the research team signalling a new participant. Participants will be remunerated for their time in line with community standards.

**Table 1 tab1:** Eligibility criteria for Stage 1 qualitative interview participants.

Participant group	Eligibility criteria
People with intellectual disability	Eligible for screening in the NCSP (have a cervix and are aged 25 to 74 years); live in NSW; can communicate their experiences in English using either verbal or non-verbal communication (with augmentative and alternative communication tools if needed).
Family members and support people	Family member or support person (unpaid or paid, for example, disability support worker) of a person/people with intellectual disability who are eligible for screening in the NCSP; live or work in Australia; speak English.
Healthcare providers	GP or nurse working with people with intellectual disability who are eligible for cervical screening in the NCSP; practice in Australia; speak English.
Disability sector stakeholders	Senior leader in Australian disability sector organisation or government agency with an interest in provision of healthcare for people with intellectual disability; speak English.

#### Qualitative semi-structured interviews and body-mapping

2.3.2

Semi-structured interviews with participants with intellectual disability will be co-conducted in-person at a disability organisation or other venue of their choice, or online via Zoom (Version 5.0.2), and will take approximately one hour. Participants will be offered the option of an additional in-person body-mapping session which will take approximately 2 to 3 h. Semi-structured interviews with family members and support people, healthcare providers and disability sector stakeholders will be conducted online via Teams or Zoom, by telephone, or in-person, depending on their preferences and will take 30 min to one hour, depending on the breadth of information provided by the participant. The interview domains and accompanying guides for each participant group will be based on existing published studies where feasible and developed through an iterative process with feedback from our multi-disciplinary team members and Advisory Group (Table 2 provides an overview of the domains).

**Table 2 tab2:** Overview of the Stage 1 qualitative interview domains for each participant group.

Interview domains	Participants			
	People with intellectual disability	Families and support people	Healthcare providers	Disability sector stakeholders
Demographics	x	x	x	x
Professional background			x	x
Knowledge of cervical screening	x	x		
Experiences of cervical screening	x			
Supporting or delivering cervical screening		x	x	x
Facilitators and barriers to cervical screening	x	x	x	x
Perceived role of self-collection for people with intellectual disability	x	x	x	x
Unmet information and training needs	x	x	x	x

Interviews will be audio-recorded and uploaded onto a secure online University of Sydney system using the participant’s unique study pseudonym and study identification number. For participants with intellectual disability, audio-files will be transcribed verbatim, using a combination of a transcriber and Happy Scribe software (43). The names of places and people identified in the interview, such as a local GP practice or healthcare provider, will not be transcribed and referred to only in general terms to further protect the anonymity of the participant. Integrity checking will be carried out for each transcription by the research team.

##### Qualitative data analysis

2.3.2.1

The sample sizes for the semi-structured interviews will be informed by information power (44). A high level of information power will be identified when a highly rigorous process of analysis has been applied (analytical sufficiency) and the richness of the information generated is sufficient to answer the study aims (data sufficiency). The appraisal of information power will include a detailed review of the first three interviews delivered within each of the four participant groups (*n* = 12 interviews) by the chief investigators with extensive qualitative expertise. The expert chief investigators will then provide detailed feedback to the research team about whether the interviews are highly relevant for the research question and add new knowledge to the field. They will continuously review the quality of the dialogues, or at least monthly, before closing data collection. Reflexive thematic analyses of the interview responses will include a process of familiarisation with the transcripts, generation of codes and coding trees and the construction of overarching themes, followed by review and categorisation of key themes (45, 46). Reflexivity will be facilitated through ongoing group discussion, listening exercises and through team members being invited to take part in a body-mapping exercise, to understand the experience of participants. We will use NVivo (Version 14) software to facilitate coding of participants’ responses. To support accessibility, discussion of themes will be facilitated by Miro, a digital collaboration platform.^1^

#### Co-production workshops

2.3.3

Stage 1 qualitative interview findings will be used to inform a series of initial and follow-up co-production workshops. All participants will be remunerated in line with community standards.

**Co-production of an accessible cervical screening resource for people with intellectual disability**
The resource for people with intellectual disability will be multimodal, incorporating Easy Read information and video materials to support accessibility for people with high support needs. It will build on the Family Planning Australia *Just Checking* resource series (47) which supports cancer screening for people with intellectual disability, their families and support people. Initial and follow-up co-production workshops (one of each in a metropolitan and a regional setting) with approximately 8 to 10 people with intellectual disability, each lasting approximately 4 h, will be facilitated by Family Planning Australia team members and the expert disability researchers. The initial workshops will set the scene about why cervical screening is important and explore how the existing resources could best be adapted to fit current community needs. Follow-up workshops with the same participants will gain feedback following resource modifications. The researchers will also collect qualitative data during the workshops through audio-recording of the group discussion. The data will be transcribed and analysed as described earlier.
**Co-production of supporting materials for families and support people**
Initial and follow-up co-production workshops with approximately 8 to 10 family members and support people will explore how these groups could use the accessible cervical screening resource in the community to support screening for people with intellectual disability. The initial workshop will explore how existing Family Planning Australia supporting materials could be adapted to meet the needs of this group. Modification of the materials will also be informed by the outcomes of the co-production workshops with people with intellectual disability, and feedback on the modified materials will be gathered at the follow-up workshop.
**Co-production of supporting materials for healthcare providers**
Trauma-informed healthcare provider training materials including extension of the existing Family Planning Australia *Supporting Decision-making Tool* (48) will developed by the clinician researchers, informed by the co-production workshop outcomes with people with intellectual disability and family members and support people. Initial and follow-up workshops will then be held with approximately 8 to 10 healthcare providers to explore how the training materials could be best used in clinical practice and determine how the training materials could be further modified to meet the needs of healthcare providers in supporting and delivering cervical screening for people with intellectual disability.

#### Development of the ScreenEQUAL website

2.3.4

An accessible ScreenEQUAL study website will be developed alongside the co-produced materials, informed by the co-production workshops and with input from the Advisory Group. It will be used to house the study materials and news items relevant to the study.

### Stage 2 methods and analysis – main trial and sub-studies

2.4

#### Main trial participants – people with intellectual disability

2.4.1

People with intellectual disability will be eligible for participation in the single-arm main trial if they are due or overdue for cervical screening in the NCSP (age 25 to 74 years with a cervix) and can communicate verbally or non-verbally including through augmentative and alternative communication (Figure 2). Participation in Stage 1 will preclude participation in Stage 2 to reduce the chance of trial participants having enhanced knowledge of cervical screening prior to the intervention (Table 3). A separate consent process will seek permission for the research team to access participants’ cervical screening histories from the Cancer Institute NSW Cancer Screening Register at a 9-month timepoint after the trial. Participants who do not consent to their screening history being accessed, will not be excluded from the trial. Participant recruitment and processes for gaining informed consent are outlined in Section 2.1.3.

**Table 3 tab3:** Eligibility criteria for Stage 2 main trial and single-arm sub-study participants.

Participant group	Eligibility criteria
People with intellectual disability	Person with intellectual disability; due or overdue for cervical screening in the NCSP (age 25 to 74 years with a cervix); can communicate verbally or non-verbally (including through augmentative and alternative communication); has not participated in Stage 1 of the study
Family members and support people	Family member or support person (unpaid or paid, for example, disability support worker) of a person/people with intellectual disability who are eligible for screening in the NCSP; live or work in Australia; speak English.
Healthcare providers	GP or nurse who works with people with intellectual disability who are eligible for screening in the NCSP; practice in Australia; speak English.

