qualitatively exploring cervical screening facilitators and barriers for people with intellectual disability as perceived by people with intellectual disability themselves, their family members and support people, healthcare providers and disability sector stakeholders;co-producing an accessible information resource to support cervical screening, including the option of self-collection, for people with intellectual disability;co-producing accompanying supporting materials for families and support people to use when sharing the accessible screening resource with people with intellectual disability;co-producing trauma-informed training materials for healthcare providers.

The Stage 2 objectives are to evaluate the co-produced study outputs (b,c,d) through a single-arm main trial with participants with intellectual disability, and single-arm sub-studies with family members and support people, and healthcare providers.

Figures 1, 2 provide an overview of Stages 1 and 2 of the study, and the study timeline is shown in Figure 3.

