#### Sub-study participants and study design – families and support people

2.4.5

Family members and support people of people with intellectual disability will be recruited into a single-arm sub-study (*n* = 48; see Table 3 for eligibility criteria). Over a 4-month timeframe this group will receive the co-produced accessible cervical screening resource and accompanying supporting materials about how it can be used to support people with intellectual disability to undertake cervical screening (the intervention). These resources will be housed on the ScreenEQUAL website, and their use will be tracked by fit-for-purpose methods including Google Analytics. Participants will be invited to complete pre-post surveys delivered online, by mail, or in-person, depending on their preference. A subset of participants (*n* ≈ 20 or until saturation is reached) will be invited to join post-intervention qualitative interviews. The surveys and interview domains will be informed by existing surveys, Stage 1 outputs and the Advisory Group, and will be piloted by family members and support people prior to the trial.

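### Section 2.4.1 and Table 3 disagree on who is barred by Stage 1 participation; under the table, workshop members who helped shape the materials could enter the sub-studies that evaluate them

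*Protocol article*

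**What the plan says.** Section 2.4.1, headed for the main trial participants, states: "Participation in Stage 1 will preclude participation in Stage 2 to reduce the chance of trial participants having enhanced knowledge of cervical screening". It then cites Table 3. Section 1 sets out what Stage 2 evaluates: a "single-arm main trial with participants with intellectual disability, and single-arm sub-studies with family members and support people, and healthcare providers".

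Table 3 gives eligibility for the main trial and both sub-studies:

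- People with intellectual disability: the row includes "has not participated in Stage 1 of the study".
- Family members and support people: a family member or paid or unpaid support person "of a person/people with intellectual disability who are eligible for screening in the NCSP; live or work in Australia; speak English". There is no Stage 1 criterion.
- Healthcare providers: "GP or nurse who works with people with intellectual disability who are eligible for screening in the NCSP; practice in Australia; speak English". There is no Stage 1 criterion.

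Sections 2.4.5 and 2.4.6 send the reader to Table 3 and add no exclusion of their own.

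In Stage 1 (section 2.3.3) the materials are shaped with members of these two groups: "Initial and follow-up co-production workshops with approximately 8 to 10 family members and support people", and "Initial and follow-up workshops will then be held with approximately 8 to 10 healthcare providers". Separately, section 2.4.5 says that the surveys and interview domains "will be piloted by family members and support people prior to the trial", and section 2.4.6 says the same for providers.

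**The concern.** The protocol gives its own reason for the exclusion: people who took part in Stage 1 may know more before the intervention than a new participant would. That reason applies at least as strongly to the sub-studies. A member of the family/support or provider workshops has discussed the materials at an initial session and commented on them again at a follow-up session. If that person then joins the sub-study, the pre survey comes after exposure, and the acceptability, feasibility and usability ratings (section 2.5.1) are partly of the person's own work.

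The two effects run in opposite directions. A raised baseline tends to shrink the pre-post change in health literacy, knowledge, attitudes, self-efficacy or preparedness. Authorship tends to lift the acceptability ratings. With a single arm there is no comparison group in which either effect would show. The limitations in the Discussion mention awareness shared through Stage 1 networks for the main trial, and self-selection of providers, but not direct Stage 1 participation by people in the sub-studies.

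**Working it through.** **Scope of the exclusion, side by side**

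| Place | Who is barred by Stage 1 participation |
|---|---|
| Section 2.4.1, sentence read literally, with Stage 2 as in section 1 | All three groups |
| Section 2.4.1, read with its heading and its reference to trial participants | People with intellectual disability |
| Table 3 | People with intellectual disability only |
| Sections 2.4.5 and 2.4.6 | Nothing beyond Table 3 |

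On the literal reading, Table 3 omits the rule from two of three rows. On the narrow reading, workshop members may enter the sub-studies. Either way, a recruiter working from Table 3 would admit them.

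**Reproducing the plan's sample sizes**

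Inputs: SD 0.5, zero pre-post correlation, power 80% and alpha 5% (section 2.4.3); two-sided testing (section 2.5.2); a change of 0.30 for families and support people, read as 30 percentage points as in the main trial, and 0.65 to 0.75 for providers (section 2.4.7).

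n = [(1.960 + 0.842) × 0.5 × √2 / change]²

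- Change 0.30: n = 43.6, rounded up to 44, as stated.
- Change 0.10: n = 392.4, rounded up to 393, as stated.
- Recruited totals: 44 × 1.1 = 48.4 (stated 48) and 393 × 1.1 = 432.3 (stated 433).

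**Worst-case illustration**

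Assumptions, none of them given in the documents: all 8 to 10 workshop members of a group enter its sub-study; they show no pre-post change; everyone else shows the planned change; their share among completers equals their share among recruits.

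Share = k / N. Diluted change = planned change × (1 − share). Power = Φ(diluted change / (0.5 × √2 / √n) − 1.960).

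Families and support people (N = 48, n = 44, standard error 0.5 × √2 / √44 = 0.1066):

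- k = 0: change 0.300, power Φ(2.814 − 1.960) = 80%.
- k = 8: share 8/48 = 16.7%, change 0.250, power Φ(2.345 − 1.960) = 65%.
- k = 10: share 10/48 = 20.8%, change 0.2375, power Φ(2.228 − 1.960) = 61%.

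Healthcare providers (N = 433, n = 393, standard error 0.5 × √2 / √393 = 0.0357):

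- k = 0: change 0.100, power 80%.
- k = 8: share 1.8%, change 0.0982, power 79%.
- k = 10: share 2.3%, change 0.0977, power 78%.

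**The case against.** The strongest reply is that the sentence in 2.4.1 already bars everyone who took part in Stage 1, because it speaks of Stage 2 as a whole. A reader of Table 3 might infer that the protocol plainly permits re-entry. It does not go that far, and what is established is a mismatch between text and table. The reply does not remove the need to act, because the sub-study sections point to the table, where the rule is missing from two of three rows.

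A reader might also add the roughly 20 Stage 1 interviewees per group to the workshop members and arrive at 28 to 30 of 48, or 58% to 63% of the family/support sample. The documents do not support treating interviewees as exposed. The interviews come before co-production and inform it, so an interviewee has not seen the co-produced materials by being interviewed. Nor did pilot testers try out the materials: sections 2.4.5 and 2.4.6 pilot the surveys and interview domains. Pilot testers would have seen the questions, and the documents do not say how many there are or whether they may enrol.

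Three further replies stand in part.

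- The power loss rests on full re-entry, no change in any re-entrant, and the plan's deliberately conservative zero correlation. With a correlation of 0.3 (an assumption), the standard error is 0.5 × √(2 × 0.7) / √44 = 0.0892, and power at a 25-point change is Φ(2.803 − 1.960), about 80%.
- Dilution works against showing a benefit, so it would not create a false positive on the pre-post outcomes. It does not answer the concern about acceptability ratings, which run the other way.
- These are secondary outcomes. Section 2.6 ties release to the resources being both effective and acceptable, and acceptability also draws on interviews and tracked website use. An inflated survey rating would not decide release alone.

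**Conclusion.** The point holds as a contradiction in scope between section 2.4.1 and Table 3 that should be settled before the sub-studies enrol. Bias is possible, not certain, since the number of Stage 1 participants who would re-enter is not given.

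The practical weight lies with the family/support sub-study. Under the worst-case assumptions, 17% to 21% of its 48 participants would be workshop members, the 30-point change would shrink to 25.0 to 23.8 points, and power would be about 65% to 61% instead of 80%. Fewer re-entrants, some change among them or a positive pre-post correlation would all make the loss smaller. For providers the effect is negligible: about 2% of 433, with power of 78% to 79%. The possible inflation of acceptability and usability ratings cannot be sized from the documents. The main trial is not affected, because both places apply the exclusion there.

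**What to change.** Make the text and the table agree. Extend the criterion "has not participated in Stage 1 of the study" to the family/support and healthcare provider rows of Table 3, stating that it includes the co-production workshops, and add that the person has not helped to pilot the survey. Word the sentence in 2.4.1 so that it names all three groups.

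The cost is one line in each of two rows and no change to any sample size. At most about 28 to 30 people per group (about 20 interviewees plus 8 to 10 workshop members, if none overlap), plus an unstated number of pilot testers, are lost from groups recruited across Australia.

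If the team prefers not to exclude them, the protocol should say so, record Stage 1 and pilot participation for each sub-study participant, and report the pre-post and acceptability results without those participants as a sensitivity analysis.

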#### Main trial design

2.4.2

The main trial is a single-arm study aimed at evaluating the primary study outcome (a change in informed decision-making about cervical screening by people with intellectual disability). An accessible informed decision-making tool will be created based on existing tools and surveys informed by the research team, Advisory Group members with intellectual disability and experts in health literacy. The modified tool will collect data via interviews using a brief set of pre-intervention open-ended accessible questions across three domains: knowledge, attitudes to screening and intention to screen (49–52). The trial will serve as a pilot study for a larger appropriately powered validation trial.

People with intellectual disability (*n* = 48) will be invited to join one of 5 or 6 accessible workshops of approximately 10 people with intellectual disability and 2 to 3 trained support people, facilitated by members of the research team. The workshops will last approximately 2 to 3 h. Support people will be identified through Family Planning Australia networks to participate in a pre-workshop session where they will receive training according to a structured session plan on how to use the co-produced resource with people with intellectual disability. The trained support people will then use the resource with workshop participants in a way that simulates what would happen in a community setting (the intervention). Individual participants with intellectual disability will be supported to complete a brief set of pre-intervention open-ended accessible questions to assess informed decision making at the start of the workshop which will be repeated at the end of the workshop or within the next week depending on the participant’s choice. Qualitative data regarding the overall perceptions of the co-produced resource will be gathered during the workshops by the research team through audio-recording of the group discussion.

A subset of participants with intellectual disability (*n* ≈ 20 or until saturation is reached) will be invited to participate in post-intervention qualitative interviews, with the option of additional body-mapping, to provide further insights into perceptions of the resources and to support the interpretation of the study outcomes (41).

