#### Main trial sample size calculations

2.4.3

The sample size calculation is based on a difference in the proportion of people with intellectual disability making an informed decision about cervical screening pre-and-post the intervention (53). Noting that making an informed decision may not necessarily lead to a person having a screening test due to barriers such as a history of sexual assault, a baseline proportion of 20% was selected based on the last published national Australian figure of 10% screening uptake for this group (26). It was estimated that 44 participants would be needed to detect a change in the proportion (%) of those assessed as being able to make an informed decision (across the domains of knowledge, attitudes, and intention to screen) from 20% pre-intervention to 50% post-intervention, with power and alpha set at 80 and 5%, respectively. Due to the novelty of our study in terms of participants and intervention, no known estimates were available for pre-post correlation between the items in the modified informed decision-making tool or outcome variability at both time points. Consequently, a conservative approach was adopted by assuming there was zero correlation between pre-post observations measured by the modified tool and that these observations displayed maximum variability, i.e., standard deviation = 0.5 (54). Assuming a dropout rate of 10%, the adjusted sample was increased to 48.

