#### Data analysis

2.5.2

Qualitative data collection and thematic analysis will follow the principles and processes described earlier. Descriptive statistics will summarise participants’ baseline characteristics in the main trial and sub-studies. The impact of the intervention (i.e., effects) on the primary and secondary outcomes will be assessed using multivariable logistic regression modelling. This approach adjusts for the data being correlated because of the pre-and-post study design. Effects will be reported as adjusted odds ratios (ORs) with 95% Confidence Intervals (CIs). Univariable logistic analyses will be used to identify potentially confounding variables such as age and place of residence. Two-sided *p*-values less than 0.05 will be considered as significant. Stata Version 18 (StataCorp LLC, College Station, TX) will be used to analyse data.

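### The intervention is given in 5 or 6 group workshops, but the sample size and the stated analysis make no allowance for correlation within workshops, so the 80% power and 5% error rate hold only if that correlation is near zero

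*Protocol article*

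**What the plan says.** Main trial design (2.4.2) has participants join "one of 5 or 6 accessible workshops of approximately 10 people with intellectual disability and 2 to 3 trained support people". The support people attached to a workshop use the resource with its participants, the research team facilitates, and there is a group discussion. The decision-making questions are asked at the start, and again at the end of the session or within the following week.

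Main trial sample size calculations (2.4.3) derives 44 participants for a change "from 20% pre-intervention to 50% post-intervention", "with power and alpha set at 80 and 5%, respectively", and raises this to 48 for 10% dropout. It describes its approach as conservative on two grounds: "assuming there was zero correlation between pre-post observations measured by the modified tool", and that these "observations displayed maximum variability, i.e., standard deviation = 0.5". No ICC, design effect or number of workshops enters.

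Data analysis (2.5.2) specifies "multivariable logistic regression modelling. This approach adjusts for the data being correlated because of the pre-and-post study design". It adds: "Two-sided *p*-values less than 0.05 will be considered as significant". Workshop is not named as a random effect, a cluster variable or a covariate.

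**The concern.** People in one workshop share the session, the discussion, the facilitators and the two or three support people who deliver the intervention. A good or poor session can move their answers together. Their changes may then be positively correlated, and 44 people carry less information than 44 independent observations.

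The two inputs called conservative concern the variance of one person's change. They say nothing about correlation between different people in the same room. The only dependence that the analysis section names is likewise within person.

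At stake are the width of the confidence interval and the meaning of a p-value below 0.05 for the primary outcome, and the power on which the sample size rests. Dissemination of study findings (2.6) makes release for national scale-up depend on the resources being found effective, so the primary result has consequences even though 2.4.2 calls the trial a pilot.

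**Working it through.** **Inputs from the protocol.** Difference 0.50 − 0.20 = 0.30; SD 0.5 at each time; pre-post correlation 0; power 80%; alpha 5% two-sided; 44 evaluable and 48 enrolled; 5 or 6 workshops. Completers after 10% dropout: 48 × 0.9 = 43.2, taken as 43, or 8.6 per workshop (five) or 7.17 (six).

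**Assumption.** The protocol gives no ICC. I use 0.02, 0.05 and 0.10 for the pre-post change.

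**Reproducing the plan's figure.** The variance of the change is 0.25 + 0.25 − 0 = 0.50. Then n = (1.960 + 0.842)² × 0.50 / 0.30² = 43.6, so 44. Power is 80.4% at 44 and 79.4% at 43. The plan's number is reproduced with no clustering term.

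**Adding the workshop.** Design effect DE = 1 + (m − 1) × ICC, where m is the workshop size; effective n = 43/DE; power = Φ(0.30/√(V/effective n) − 1.96). V is 0.50 (the plan) or 0.20 × 0.80 + 0.50 × 0.50 = 0.41 (the binomial variance at the plan's own 20% and 50%). The error rate of a nominal 5% test that ignores workshop is 2 × (1 − Φ(1.96/√DE)).

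| Workshops | ICC | DE | Power, V = 0.50 | Power, V = 0.41 | Error rate ignoring workshop |
|---|---|---|---|---|---|
| 5 | 0.02 | 1.15 | 74% | 82% | 6.8% |
| 5 | 0.05 | 1.38 | 66% | 74% | 9.5% |
| 5 | 0.10 | 1.76 | 55% | 64% | 14.0% |
| 6 | 0.02 | 1.12 | 75% | 83% | 6.4% |
| 6 | 0.05 | 1.31 | 68% | 77% | 8.7% |
| 6 | 0.10 | 1.62 | 59% | 68% | 12.3% |

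**Binary simulation of the error rate.** 40,000 runs per setting; 44 participants; 20% before and after; no within-person correlation; workshop ICC on the post measure only. A test ignoring workshop rejected in 6.1 to 6.3% of runs at ICC 0.02, 7.3 to 7.9% at 0.05 and 9.3 to 10.4% at 0.10 (six to five workshops). At ICC 0 it rejected in 5.2 to 5.4%. These rates are lower than the table's largely because an ICC of 0.10 on the post measure alone is 0.10 × 0.16/(0.16 + 0.16) = 0.05 on the change.

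**Cost of a workshop-level test.** A t test on the workshop mean changes has 4 or 5 degrees of freedom, with critical values 2.776 and 2.571 against 1.960. With 43 completers and V = 0.50, its power at ICC 0 is already only about 56% (five workshops) or 61% (six). At ICC 0.05 it is about 44% or 50%.

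**The case against.** **The conservative inputs may cover the power loss.** Much of this stands. With V = 0.41 and an assumed pre-post correlation of 0.2, the variance is 0.41 − 2 × 0.2 × 0.4 × 0.5 = 0.33. Five-workshop power is then 89%, 83% and 73% at the three ICCs. With a correlation of 0.3 it is 93%, 88% and 79% (rounded from 92.6, 87.5 and 78.6). None of this helps the error rate, because a generous planning variance does not correct a standard error that ignores workshop.

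**The ICC may be small.** Also fair. Only the ICC of the change matters, so baseline similarity within a workshop partly cancels. Support people are trained to a structured session plan, and each participant answers individually. Nothing in the protocol supports any particular value, including zero.

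**A statistical analysis plan may add a workshop term.** It may, and the article does not exclude one. The power statement, however, is fixed in 2.4.3 without clustering, and 2.5.2 names one source of correlation only.

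**Stronger readings to avoid.** A reader might infer that the trial is shown to be underpowered, or that its true error rate is 14%. The documents support neither: both depend on an ICC that they do not give, and 14% is the top of an assumed range under one formula. A reader might also take the abandoned cluster-randomised design (2.1.2) as having settled the question. Those clusters were healthcare providers with the people they serve; the workshops remain.

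**Conclusion.** The omission is certain; its size is conditional. For any positive ICC of the change, an analysis without workshop is too optimistic about precision and exceeds the 5% error rate. Over ICC 0.02 to 0.10 the excess is modest to material: about 6 to 10% in the simulation and up to 14% by the normal formula. This is the firmer half of the point.

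The power half is weaker. Under the plan's own variance, five-workshop power falls from about 80% to between 74% and 55%. With the binomial variance and no pre-post correlation, it stays at or above 80% only up to an ICC of about 0.03. Positive pre-post correlation extends that margin. The word conservative is therefore justified for small ICCs and not in general. The point should be addressed, but it does not undermine the design.

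**What to change.** 1. Account for workshop in the analysis of the primary outcome. One way is a workshop random effect with a small-sample correction; ordinary cluster-robust standard errors are unreliable with 5 or 6 clusters. At the least, pre-specify a sensitivity analysis based on the workshop mean changes, and base the conclusion on both results. State the cost: with 4 or 5 degrees of freedom the workshop-level interval is markedly wider, and power is about 56% or 61% even at ICC 0.
2. In 2.4.3, replace the unqualified 80% power and the conservative label with power over a stated ICC range, computed for the analysis that will be used. The table above uses the normal cut-off and would overstate the power of a small-sample method.
3. Prefer six workshops of about 8 (48/6), which the protocol's wording already allows. The gain is modest: 68% against 66% at ICC 0.05 under the plan's variance, and 61% against 56% for the workshop-level test at ICC 0. The protocol does not describe the resources for a sixth workshop, so its feasibility needs confirming.

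Reporting the estimated ICC is optional. With five workshops of nine, an estimate of 0.05 would have a 95% interval of roughly −0.06 to 0.56.

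These are changes to the analysis and the sample-size wording, made before data collection. They need no more participants. The price is a less favourable power statement and wider intervals.
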